**Data management of genotype data**

Exploratory genotype data generated in this study will be stored in the AstraZeneca genotyping LIMS database, or other appropriate secure system within AstraZeneca and/or third party contracted to work with AstraZeneca to analyse samples.

Some or all of the clinical datasets from the main study may be merged with the genetic data in a suitable secure environment separate from the clinical database.

**Data associated with human biological samples**

Data associated with biological samples will be transferred from laboratory (ies) internal or external to AstraZeneca.

Management of external data

Data from external providers (e.g. central laboratories) will be validated as appropriate to ensure it is consistent with the clinical data and included in the final database.Tumour tissue or blood for exploratory analyses data, the results of any analyses will not be recorded in the database, but information relating to the processing of the sample, including the original date of biopsy (historical tumour tissue sample and the actual date the sample(s) were collected) will be recorded in the eCRF and database.

# Ethical and regulatory requirements

## Ethical conduct of the study

The study will be performed in accordance with ethical principles that have their origin in the Declaration of Helsinki and are consistent with International Conference on Harmonisation (ICH)/Good Clinical Practice (GCP), applicable regulatory requirements and the AstraZeneca policy on Bioethics and Human Biological Samples.

## Patient data protection

The Informed Consent Form will incorporate (or, in some cases, be accompanied by a separate document incorporating) wording that complies with relevant data protection and privacy legislation.

## Ethics and regulatory review

An Ethics Committee (EC) should approve the final study protocol, including the final version of the Informed Consent Form and any other written information and/or materials to be provided to the patients. The Investigator will ensure the distribution of these documents to the applicable Ethics Committee, and to the study site staff.

The opinion of the Ethics Committee should be given in writing. The Investigator should submit the written approval to AstraZeneca before enrolment of any patient into the study.

The Ethics Committee should approve all advertising used to recruit patients for the study.

AstraZeneca should approve any modifications to the Informed Consent Form that are needed to meet local requirements.

If required by local regulations, the protocol should be re-approved by the Ethics Committee annually.

Before enrolment of any patient into the study, the final study protocol, including the final version of the Informed Consent Form, is approved by the national regulatory authority or a notification to the national regulatory authority is done, according to local regulations.

AstraZeneca will handle the distribution of any of these documents to the national regulatory authorities.

AstraZeneca will provide Regulatory Authorities, Ethics Committees and Principal Investigators with safety updates/reports according to local requirements.

Each PI is responsible for providing the Ethics Committees/IRB with reports of any serious and unexpected adverse drug reactions from any other study conducted with the investigational product. AstraZeneca will provide this information to the PI so that he/she can meet these reporting requirements.

## Informed consent

The Principal Investigator(s) at each centre will:

Ensure each patient is given full and adequate oral and written information about the nature, purpose, possible risk and benefit of the study

Ensure each patient is notified that they are free to discontinue from the study at any time

Ensure that each patient is given the opportunity to ask questions and allowed time to consider the information provided

Ensure each patient provides signed and dated informed consent before conducting any procedure specifically for the study

Ensure the original, signed Informed Consent Form(s) is/are stored in the Investigator’s Study File

Ensure a copy of the signed Informed Consent Form is given to the patient

Ensure that any incentives for patients who participate in the study as well as any provisions for patients harmed as a consequence of study participation are described in the informed consent form that is approved by an Ethics Committee.

## Changes to the protocol and informed consent form

Study procedures will not be changed without the mutual agreement of the International co-ordinating Investigator, the Principal Investigator and AstraZeneca or designated CRO.

If there are any substantial changes to the study protocol, then these changes will be documented in a study protocol amendment and where required in a new version of the study protocol (Revised Clinical Study Protocol).

The amendment is to be approved by the relevant Ethics Committee and if applicable, also the national regulatory authority approval, before implementation. Local requirements are to be followed for revised protocols.

AstraZeneca or designated CRO will distribute any subsequent amendments and new versions of the protocol to each Principal Investigator(s). For distribution to Ethics Committee see Section 10.3.

If a protocol amendment requires a change to a centre’s Informed Consent Form, AstraZeneca and the centre’s Ethics Committee are to approve the revised Informed Consent Form before the revised form is used.

If local regulations require, any administrative change will be communicated to or approved by each Ethics Committee.

## Audits and inspections

Authorised representatives of AstraZeneca, a regulatory authority, or an Ethics Committee may perform audits or inspections at the centre, including source data verification. The purpose of an audit or inspection is to systematically and independently examine all study-related activities and documents, to determine whether these activities were conducted, and data were recorded, analysed, and accurately reported according to the protocol, Good Clinical Practice (GCP), guidelines of the International Conference on Harmonisation (ICH), and any applicable regulatory requirements. The Investigator will contact AstraZeneca immediately if contacted by a regulatory agency about an inspection at the centre.

Appendix A Additional Safety Information

Further Guidance on the Definition of a Serious Adverse Event (SAE)

Life threatening

‘Life-threatening’ means that the patient was at immediate risk of death from the AE as it occurred or it is suspected that use or continued use of the product would result in the patient’s death. ‘Life-threatening’ does not mean that had an AE occurred in a more severe form it might have caused death (eg, hepatitis that resolved without hepatic failure).

Hospitalisation

Outpatient treatment in an emergency room is not in itself a serious AE, although the reasons for it may be (eg, bronchospasm, laryngeal oedema). Hospital admissions and/or surgical operations planned before or during a study are not considered AEs if the illness or disease existed before the patient was enrolled in the study, provided that it did not deteriorate in an unexpected way during the study.

Important medical event or medical intervention

Medical and scientific judgement should be exercised in deciding whether a case is serious in situations where important medical events may not be immediately life threatening or result in death, hospitalisation, disability or incapacity but may jeopardize the patient or may require medical intervention to prevent one or more outcomes listed in the definition of serious. These should usually be considered as serious.

Simply stopping the suspect drug does not mean that it is an important medical event; medical judgement must be used.

- Angioedema not severe enough to require intubation but requiring iv hydrocortisone treatment
- Hepatotoxicity caused by paracetamol (acetaminophen) overdose requiring treatment with N-acetylcysteine
- Intensive treatment in an emergency room or at home for allergic bronchospasm
- Blood dyscrasias (eg, neutropenia or anaemia requiring blood transfusion, etc) or convulsions that do not result in hospitalisation
- Development of drug dependency or drug abuse

A Guide to Interpreting the Causality Question

When making an assessment of causality consider the following factors when deciding if there is a ‘reasonable possibility’ that an AE may have been caused by the drug.

- Time Course. Exposure to suspect drug. Has the patient actually received the suspect drug? Did the AE occur in a reasonable temporal relationship to the administration of the suspect drug?
- Consistency with known drug profile. Was the AE consistent with the previous knowledge of the suspect drug (pharmacology and toxicology) or drugs of the same pharmacological class? Or could the AE be anticipated from its pharmacological properties?
- De-challenge experience. Did the AE resolve or improve on stopping or reducing the dose of the suspect drug?
- No alternative cause. The AE cannot be reasonably explained by another aetiology such as the underlying disease, other drugs, other host or environmental factors.
- Re-challenge experience. Did the AE reoccur if the suspected drug was reintroduced after having been stopped? AstraZeneca would not normally recommend or support a re-challenge.
- Laboratory tests. A specific laboratory investigation (if performed) has confirmed the relationship.

In difficult cases, other factors could be considered such as:

- Is this a recognized feature of overdose of the drug?
- Is there a known mechanism?

Causality of ‘related’ is made if following a review of the relevant data, there is evidence for a ‘reasonable possibility’ of a causal relationship for the individual case. The expression ‘reasonable possibility’ of a causal relationship is meant to convey, in general, that there are facts (evidence) or arguments to suggest a causal relationship.

The causality assessment is performed based on the available data including enough information to make an informed judgment. With limited or insufficient information in the case, it is likely that the event(s) will be assessed as ‘not related’.

Causal relationship in cases where the disease under study has deteriorated due to lack of effect should be classified as no reasonable possibility.

Appendix B Actions Required in Cases of Increases in Liver

Biochemistry and Evaluation of Hy’s Law

Introduction

This Appendix describes the process to be followed in order to identify and appropriately report cases of Hy’s Law. It is not intended to be a comprehensive guide to the management of elevated liver biochemistries.

During the course of the study the Investigator will remain vigilant for increases in liver biochemistry. The investigator is responsible for determining whether a patient meets potential Hy’s Law (PHL) criteria at any point during the study.

The Investigator participates, together with AstraZeneca clinical project representatives, in review and assessment of cases meeting PHL criteria to agree whether Hy’s Law (HL) criteria are met. HL criteria are met if there is no alternative explanation for the elevations in liver biochemistry other than Drug Induced Liver Injury (DILI) caused by the Investigational Medicinal Product (IMP).

The Investigator is responsible for recording data pertaining to PHL/HL cases and for reporting Adverse Events (AE) and Serious Adverse Events (SAE) according to the outcome of the review and assessment in line with standard safety reporting processes.

Definitions

Potential Hy’s Law (PHL)

Aspartate Aminotransferase (AST) or Alanine Aminotransferase (ALT) ≥ 3x Upper Limit of Normal (ULN) **together with** Total Bilirubin (TBL) ≥ 2xULN at any point during the study following the start of study medication irrespective of an increase in Alkaline Phosphatase (ALP).

Hy’s Law (HL)

AST or ALT ≥ 3x ULN **together with** TBL ≥ 2xULN, where no other reason, other than the IMP, can be found to explain the combination of increases, eg, elevated ALP indicating cholestasis, viral hepatitis, another drug.

For PHL and HL the elevation in transaminases must precede or be coincident with (i.e. on the same day) the elevation in TBL, but there is no specified timeframe within which the elevations in transaminases and TBL must occur.

Identification of Potential Hy’s Law Cases

In order to identify cases of PHL it is important to perform a comprehensive review of laboratory data for any patient who meets any of the following identification criteria in isolation or in combination:

- ALT ≥ 3xULN
- AST ≥ 3xULN
- TBL ≥ 2xULN

When the identification criteria are met from central or local laboratory results the Investigator will without delay:

- Determine whether the patient meets PHL criteria (see Definitions within this Appendix for definition) by reviewing laboratory reports from all previous visits (including both central and local laboratory results)

The Investigator will without delay review each new laboratory report and if the identification criteria are met will:

- Notify the AstraZeneca representative
- Determine whether the patient meets PHL criteria (see Definitions within this Appendix for definition) by reviewing laboratory reports from all previous visits
- Promptly enter the laboratory data into the laboratory CRF

Follow-up

Potential Hy’s Law Criteria not met

If the patient does not meet PHL criteria the Investigator will:

- Inform the AstraZeneca representative that the patient has not met PHL criteria.
- Perform follow-up on subsequent laboratory results according to the guidance provided in the Clinical Study Protocol.

Potential Hy’s Law Criteria met

If the patient does meet PHL criteria the Investigator will:

- Determine whether PHL criteria were met at any study visit prior to starting study treatment (See Actions Required When Potential Hy’s Law Criteria are Met Before and After Starting Study Treatment)
- Notify the AstraZeneca representative who will then inform the central Study Team

The Study Physician contacts the Investigator, to provide guidance, discuss and agree an approach for the study patients’ follow-up and the continuous review of data. Subsequent to this contact the Investigator will:

- Monitor the patient until liver biochemistry parameters and appropriate clinical symptoms and signs return to normal or baseline levels, or as long as medically indicated
- Investigate the etiology of the event and perform diagnostic investigations as discussed with the Study Physician.
- Complete the three Liver CRF Modules as information becomes available
- If at any time (in consultation with the Study Physician) the PHL case meets serious criteria, report it as an SAE using standard reporting procedures

Review and Assessment of Potential Hy’s Law Cases

The instructions in this Section should be followed for all cases where PHL criteria are met.

No later than 3 weeks after the biochemistry abnormality was initially detected, the Study Physician contacts the Investigator in order to review available data and agree on whether there is an alternative explanation for meeting PHL criteria other than DILI caused by the IMP.

According to the outcome of the review and assessment, the Investigator will follow the instructions below.

If there is an agreed alternative explanation for the ALT or AST and TBL elevations, a determination of whether the alternative explanation is an AE will be made and subsequently whether the AE meets the criteria for a SAE:

- If the alternative explanation is **not** an AE, record the alternative explanation on the appropriate CRF
- If the alternative explanation is an AE/SAE, record the AE /SAE in the CRF accordingly and follow the AZ standard processes

If it is agreed that there is **no** explanation that would explain the ALT or AST and TBL elevations other than the IMP:

- Report an SAE (report term ‘Hy’s Law’) according to AstraZeneca standard processes.
- The ‘Medically Important’ serious criterion should be used if no other serious criteria apply
- As there is no alternative explanation for the HL case, a causality assessment of ‘related’ should be assigned.

If, there is an unavoidable delay, of over 3 weeks, in obtaining the information necessary to assess whether or not the case meets the criteria for HL, then it is assumed that there is no alternative explanation until such time as an informed decision can be made:

- Report an SAE (report term ‘Potential Hy’s Law’) applying serious criteria and causality assessment as per above
- Continue follow-up and review according to agreed plan. Once the necessary supplementary information is obtained, repeat the review and assessment to determine whether HL criteria are met. Update the SAE report according to the outcome of the review

Actions Required When Potential Hy’s Law Criteria are Met Before and After Starting Study Treatment

This section is applicable to patients with liver metastases who meet PHL criteria on study treatment having previously met PHL criteria at a study visit prior to starting study treatment.

At the first on study treatment occurrence of PHL criteria being met the Investigator will:

- Determine if there has been a significant change in the patients’ condition^#^ compared with the last visit where PHL criteria were met^#^
- If there is no significant change no action is required
- If there is a significant change notify the AstraZeneca representative, who will inform the central Study Team, then follow the subsequent process described in Potential Hy’s Law Criteria met of this Appendix

^#^ A ‘significant’ change in the patient’s condition refers to a clinically relevant change in any of the individual liver biochemistry parameters (ALT, AST or total bilirubin) in isolation or in combination, or a clinically relevant change in associated symptoms. The determination of whether there has been a significant change will be at the discretion of the Investigator, this may be in consultation with the Study Physician if there is any uncertainty.

Actions Required for Repeat Episodes of Potential Hy’s Law

This section is applicable when a patient meets PHL criteria on study treatment and has already met PHL criteria at a previous on study treatment visit.

The requirement to conduct follow-up, review and assessment of a repeat occurrence(s) of PHL is based on the nature of the alternative cause identified for the previous occurrence.

The investigator should determine the cause for the previous occurrence of PHL criteria being met and answer the following question:

- Was the alternative cause for the previous occurrence of PHL criteria being met found to be the disease under study e.g. chronic or progressing malignant disease, severe infection or liver disease, << or did the patient meet PHL criteria prior to starting study treatment and at their first on study treatment visit as described in Actions Required When Potential Hy’s Law Criteria are Met Before and After Starting Study Treatment >>?

If No: follow the process described in Potential Hy’s Law Criteria met of this Appendix

If Yes:

Determine if there has been a significant change in the patient’s condition^#^ compared with when PHL criteria were previously met

- If there is no significant change no action is required
- If there is a significant change follow the process described in this Appendix

^#^ A ‘significant’ change in the patient’s condition refers to a clinically relevant change in any of the individual liver biochemistry parameters (ALT, AST or total bilirubin) in isolation or in combination, or a clinically relevant change in associated symptoms. The determination of whether there has been a significant change will be at the discretion of the Investigator; this may be in consultation with the Study Physician if there is any uncertainty.

References

FDA Guidance for Industry (issued July 2009) ‘Drug-induced liver injury: Premarketing clinical evaluation’: <http://www.fda.gov/downloads/Drugs/GuidanceComplianceRegulatoryInformation/Guidances/UCM174090.pdf>

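### Appendix B can exempt a repeat potential Hy's Law episode from the dedicated liver review because of an earlier, possibly resolved cause, and it lists severe infection and liver disease as examples of the disease under study

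*Protocol*

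**What the plan says.** Protocol Appendix B, under Actions Required for Repeat Episodes of Potential Hy's Law, covers a patient who meets PHL criteria on treatment and "has already met PHL criteria at a previous on study treatment visit". Whether the new episode must be followed up, reviewed and assessed "is based on the nature of the alternative cause identified for the previous occurrence".

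The investigator asks whether that earlier cause was "found to be the disease under study e.g. chronic or progressing malignant disease, severe infection or liver disease". A second clause, about patients who met PHL criteria before treatment, follows inside unresolved << >> markers.

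- If the answer is no, the full PHL process applies.
- If the answer is yes, the investigator looks for a significant change "compared with when PHL criteria were previously met". Where there is one, the Appendix B process is followed. Otherwise: "If there is no significant change no action is required".

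The footnote defines a significant change as a clinically relevant change in ALT, AST or total bilirubin, or in associated symptoms. The judgement is left to the investigator; consulting the Study Physician is optional.

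Three other parts of Appendix B bear on this:

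- Follow-up of a PHL case includes the instruction "Monitor the patient until liver biochemistry parameters and appropriate clinical symptoms and signs return to normal or baseline levels", or for as long as medically indicated.
- The section on review and assessment states that its instructions apply to every case meeting PHL criteria.
- Hy's Law is defined as the raised transaminase and bilirubin values "where no other reason, other than the IMP, can be found to explain the combination of increases".

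**The concern.** The rule decides whether to look for the cause of a new episode by asking what caused the old one. That is understandable when the old cause persists. The preceding section of Appendix B makes a similar comparison, but only for patients with liver metastases. It is not sound when the old cause was transient and has cleared, and severe infection is usually such a cause.

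The label is also wrong for this trial. The disease under study is ovarian cancer (Protocol sections 1.5 and 6.3.10). Active uncontrolled infection and known active hepatitis are exclusion criteria (section 3.2), so these causes would mostly be new events arising during the study. The leftover markers suggest template text that was not adapted.

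Appendix B exists to identify and report Hy's Law cases. Under this branch, a second episode caused by olaparib could miss the one procedure designed to decide whether it is such a case.

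**Working it through.** The plan gives no figure here and no arithmetic applies. The check traces the rule through one scenario and then sets the passages side by side.

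**Scenario.** A patient on olaparib has a first PHL episode attributed to severe infection. The infection clears and liver values return to baseline. Later, still on treatment, she meets PHL criteria again, with similar ALT, AST and bilirubin and similar symptoms.

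1. *First episode.* The full process applies: follow-up to normal or baseline, a search for the cause, and a review with the Study Physician within three weeks. An alternative explanation is agreed.
2. *Second episode, identification step.* Appendix B requires each new laboratory report that meets the identification criteria to be notified to the sponsor's representative, checked against PHL criteria and entered in the CRF. This still happens.
3. *Second episode, question on the previous cause.* Severe infection is on the list, so the answer is yes.
4. *Comparison.* The reference is the first episode, not the recovered values. Values and symptoms are similar, so there is no significant change.
5. *Outcome.* No action is required. Nothing in this branch asks whether the infection is still present or what caused the second episode.

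**Same second episode, different history.** Had the first episode been attributed to another drug, the answer at step 3 would be no and the full process would apply. Had the comparison been with the recovered values, the second episode would be a clinically relevant change and would also enter the process. Identical findings are handled differently because of the earlier label and the choice of reference.

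**Side by side within Appendix B.**

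| Part of Appendix B | What it implies for the second episode |
| --- | --- |
| Review and assessment | Applies to every case meeting PHL criteria; no exception is stated |
| Definition of Hy's Law | Requires that no other reason for these increases can be found, so a reason has to be sought |
| Delay of more than three weeks in obtaining information | No alternative explanation is assumed, and an SAE is reported, until an informed decision can be made |
| Repeat-episode branch | No review if the previous cause is listed and the values and symptoms look alike |

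The first three rows lead to an assessment of the current episode or, failing that, to a provisional assumption against the drug. The fourth carries an old explanation forward without checking it.

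**The case against.** The strongest reply is that little is lost.

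- **Other reporting routes stay open.** Besides the notification and data entry at step 2, Protocol section 6.3.6 has mandated laboratory results summarised in the study report and allows deterioration to be reported as an AE. Section 6.3.4 requires a causality answer for each AE. Section 6.3.7 says the combined elevation may need SAE reporting, and section 6.4 requires all SAEs to be reported. This stands. A reader might infer that an exempted repeat means no SAE, no causality assessment and no entry in the liver data; the documents do not support that. These routes are only partial substitutes: section 6.3.6 makes a mandated laboratory deterioration an AE only under listed conditions, one of which is the investigator's belief that it should be reported.
- **Symptoms count as change.** An episode with infection and one without will often differ in symptoms, and the investigator may then start the full process. This also stands, and it narrows the gap to similar values with similar symptoms.
- **The repeat section may be a deliberate exception to the general rule.** Possibly, but the review section states no exception, and an exception for the disease under study should not extend to causes that are not that disease.
- **The examples may be meant loosely, as alternative causes in general.** The grammar places them under the disease under study. Chronic liver disease can plausibly explain repeated elevations, but that would have to be stated as its own category.

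Two further inferences fail. A reader might treat the recurrence as a positive re-challenge, since Appendix A asks "Did the AE reoccur if the suspected drug was reintroduced after having been stopped". The scenario involves no stopping and restarting of olaparib, so that criterion does not apply. A reader might also size the problem from the planned 220 patients: no cases gives a one-sided 95% upper limit of 1 − 0.05^(1/220) = 1.35%, and one case is 1/220 = 0.45%. The arithmetic is right, but it holds for any rare event in 220 patients and does not show how often this branch would be reached.

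**Conclusion.** The point holds in a limited form. As written, the repeat-episode branch can exempt a new PHL episode from the dedicated process because of a previous cause that has resolved. It also names causes that are not the disease under study, and it conflicts with the scope of the review section and with the definition of Hy's Law. What can be lost is the PHL follow-up, the search for a cause, the three-week review and the Hy's Law causality decision. The laboratory record and the ordinary AE/SAE routes remain.

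The gap opens only if the earlier on-treatment episode was attributed to a listed cause, the values recovered, the second episode resembles the first in values and symptoms, and the investigator does not escalate. That combination should be rare; the documents give no frequency and none is estimated here. Safety is a stated objective (section 2.3) and is summarised descriptively, with no liver-specific threshold, so the effect is on case ascertainment. PFS, OS and the sample size are untouched. Severity is minor to moderate.

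**What to change.** In the repeat-episode section of Appendix B:

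1. Remove from the examples the causes that are not the disease under study, and resolve the << >> markers.
2. Reconcile the no-action branch with the Hy's Law definition and with the stated scope of the review section, so that a repeat episode after recovery is not exempted from the existing PHL review because of a previous, resolved cause.

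The sponsor should settle the exact clinical wording; no particular monitoring or management rule is proposed here. The cost is a few sentences in Appendix B and at most a few extra case reviews.
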